### Screening visit

Before undergoing any study related procedure (including screening procedures), all potential participants will provide full, written informed consent. Participant demographics, full medical history including cancer history, general physical examination, and patient symptom questionnaires are completed at the screening visit. Standard of care blood tests, research blood tests and six skin swabs (Table 2) are taken, and a pregnancy test is taken for women of childbearing potential. Sites undergoing skin swab were: forehead, upper chest, upper back, dorsum of the hand and forearm; vitiligo-like depigmenting rashes were also swabbed if present. The full schedule of events is shown below in Table 2. Participants at consent can decide to contribute optional additional samples including: regular stool samples for microbiome/mycobiome analysis, accompanied by optional completion of a nutritional questionnaire, and optional gastrointestinal or dermatological tissue if they develop a SirAE affecting these sites that trigger the need for biopsy as part of routine care.

**Table 2 Tab2:** Schedule of events

VISITS	VISIT 1^a^	VISIT 2^b^	VISIT 3^b^	VISIT 4^b^	VISIT 5^b^	VISIT 6^b^	END OF STUDY VISIT^C^	Unsched-uled Visit^d^	SirAE Visit^e^	Optional ‘special case’ SirAE biopsies^f^
**TREATMENT CYCLE (Combination ipilimumab/nivolumab, single agent pembrolizumab, nivulumab or atezolizumab, or switch between these therapies or to another CPI treatment / regimen**	**CYCLE 1** **-14 days** **(Baseline)**	**CYCLE 2 +/-7 days**	**CYCLE 3 +/-7 days**	**CYCLE 4 +/-7 days**	**CYCLE** **dependent upon drug regimen** ^**b**^ **+/-7 days**	**CYCLE** dependentupon drug regimen^**b**^ **+/-7 days**				
**Procedures**										
Discuss Study	X									
Sign consent form	X^g^								X^h^	X^h^
Pregnancy test	X	X^i^	X^i^	X^i^	X^i^	X^i^	X^i^	X^i^	X^i^	X^i^
Concomitant meds recording	X	X	X	X	X	X	X	X		X
General physical examination	X	X^j^	X^j^	X^j^	X^j^	X^j^	X^j^	X^j^		X^j^
Adverse event assessment	X	X	X	X	X	X	X	X		X
Questionnaire^k^	X	X	X	X	X	X	X	X		X
Blood test (NHS Lab)^l^	X	X	X	X	X	X	X	X		X
Research blood test^m^	X	X	X	X	X	X	X		X	X
Skin swabs^n^	X	X	X	X	X		X		X	
Stool Sample (optional)^o^	X	X	X	X	X		X		X	
Photography of skin IrAEs (optional)^p^		X	X	X	X	X	X	X		
Skin Biopsy for research (optional)^q^									X	X
Endoscopic biopsies for research (consenting patients with GI SirAEs only)^r^.									X	X

a Baseline procedures should be performed within 14 days of receiving of administration of the first dose of combination ipilimumab/nivolumab, or single agent pembrolizumab, nivolumab or atezolimumab

b Study visits to occur within +/-7 days of receiving CPI for visits 2, 3, 4, 5 and 6. Cycles of CPI treatment are scheduled to occur at:

i Nivolumab (3-weekly)/ipilimumab (3- or -6 weekly) x 4 cycles, followed 6 weeks after combination treatment by 4-weekly single agent Nivolumab) (melanoma) weeks 3, 6, 9, 15 and 39 (i.e. cycles 2, 3, 4, 5 and 11)

ii Nivolumab (melanoma) weeks 4, 8, 12, 16 and 40 (i.e. cycles 2, 3, 4, 5 and 11)

iii Pembrolizumab (3-weekly, followed by 6-weekly after week 9 or 12) (melanoma), weeks 3, 6 and 9, then week 15 or 18 and week or 39 or 36 (i.e. cycles 2, 3, 4, 5 or 6 and 9)

iv. Pembrolizumab (6-weekly) (melanoma) weeks 6, 12, 18, 24 and 36 (i.e. cycles 2, 3, 4, 5 and 7)

v Pembrolizumab 4 × 3-weekly followed by 6-weekly after week 12 (NSCLC), weeks 3, 6, 9, 18 and 36 (i.e. cycles 2, 3, 4, 6 and 9)

vi Atezolizumab 4-weekly (NSCLC) weeks 4, 8, 12, 16 and 40) (i.e. cycles 2, 3, 4, 5 and 11)

vii Nivolumab(3-weekly)/ipilimumab(6-weekly) (Mesothelioma) weeks 3, 6, 9, 15 and 36 (i.e. cycles 2, 3, 4, 6 and 13)

c End of Study Visit, if applicable, i.e. if a patient’s treatment ends before completing the follow up visits and for a reason other than a SirAE Visit to be completed within 14 days of the decision to end treatment

d An unscheduled visit is only required at the discretion of the investigator if the participant contacts the research team with a new possible irAE (see *Sect. 7.6*)

e Wherever possible the SirAE visit (and all of the listed procedures except optional gut biopsy) should be combined with the scheduled or unscheduled visit at which the SirAE is determined to have occurred, unless a scheduled or unscheduled visit has already been performed within post 7 days (or 14 days if a standard of care gut or skin biopsy with a research biopsy is being performed) of identification of the SirAE (see Sect. 7.7), in which instance the SirAE procedures should be carried out alone. Some of the SirAE procedures may require a separate visit when the SirAE event can only be confirmed when blood results are available or for gastrointestinal or skin SirAEs where the patient consents to gut or skin biopsy

f Optional ‘special case’ SirAE biopsies when standard of care gut or skin biopsy occur later than 14 days post initial identification of an SirAE whilst on CPI treatment. Optional research biopsies will be allowed at any time point that standard of care biopsies occur, until what would have been the patient’s final scheduled study visit if no SirAEs had occurred. Research procedures listed in the above table will be performed on the same day as the research biopsy (if not already performed within 7 days of the biopsy)

g Main study and (optional) for stool sample donation and also (optional) for a skin biopsy where indicated

h For obtaining gut biopsies for research from patients experiencing gastrointestinal SirAEs undergoing lower gastrointestinal tract endoscopies as part of routine care under direction of consulting gastroenterologist (optional), or for a skin biopsy where indicated (optional)

i Female patients will be asked whether they might be pregnant at each study visit and a pregnancy test conducted if relevant

j Physical exam as applicable, as per standard of care

k Symptom-directed questionnaire; Appendix 1

l FBC, U&E, LFT, TFT, Magnesium (standard of care tests) ESR, CRP (non-standard of care tests). At an End of Study visit FBC to be done as a research blood, if not being done as standard of care

m 4 × 10mL EDTA, 1 × 8.5mL serum, 1 × 10mL heparin

n. Skin swabs from forehead, upper chest, upper back, dorsum of the hand and forearm at each visit with potential additional swab from a site of vitiligo-like depigmenting rash if occurs. ***Skin swabs applicable only for up to the first 53 evaluable participants***

o Only for patients who consented at baseline to stool sample collection. ***Stool collection applicable only for up to the first 53 evaluable participants***

p Only for patients who consented at baseline to photography of skin IrAEs

q Only for patients who consent to optional skin biopsy of affected skin

r Only for patients who consent at time incident IrAE determined

### Follow-up: post-cycle 1,2,3,4, and 9 months

Patients undergo formal study clinical review post-cycles 1, 2, 3, and 4 months of CPI treatment and at 9–10 months depending on the CPI regimen as detailed in Table 2 to coincide with routine care visits to hospital. If patients change CPI therapy prior to completing the scheduled 6 study visits, then they can continue within the study from cycle 1 of their new treatment until they have completed 6 scheduled study visits in total. Adverse events and concurrent medications are recorded at each visit in addition to clinical review. Clinical review will include collation of a detailed symptom directed questionnaire from patients, general physical examination, collection of skin swabs and routine blood tests. Participants who have consented to optional stool samples will also provide these following each visit, they will furthermore be asked to submit a completed dietary questionnaire.

### Adverse events and principle clinical end point

The reporting of adverse events will be undertaken at each visit, with these graded as mild, moderate, or severe, and allocation of a numerical grade according to the CTCAE version 5^2^. AEs are classified in terms of their relatedness to CPI therapy as follows: unrelated, unlikely, possible, probable, definitely and not assessable.

*Significant* IrAEs for purposes of the MEDALLION study (SirAEs) are defined according to strict criteria and recorded at scheduled/unscheduled visits, being those considered “definitely” or “probably” related to administration of the CPI therapy, and meeting organ system-specific criteria as outlined in Table 1. SirAEs constitute the principle clinical endpoint of the study.

Where a definite IrAE is determined to have occurred by the investigator but the above SirAE criteria are not fulfilled this will be recorded as a “non-significant IrAE” and the patient will remain in follow-up.

### IrAE ‘ad hoc’ visit

Participants can directly request an unscheduled visit if they suspect they are developing an IrAE, or they may be identified at routine clinical review. Research specific biological sampling will take place at the time of incident IrAE.

### Withdrawal criteria

Participants can decide to withdraw their consent at any point during the study. The clinical investigator may withdraw a participant from the trial at any time if this is considered necessary, and for any reason including:

i.Symptomatic deterioration.ii.Participant withdrawal of consent or inability (through incapacity or otherwise) to provide consent for study-specific procedures to proceed.iii.Significant protocol deviation or non-compliance, including failure to attend for > 2 consecutive visits.iv.An adverse event such that continuation of CPI therapy is no longer appropriate, even if SirAE criteria are not fulfilled.v.Termination of the clinical trial by the sponsor.vi.Investigator’s discretion that it is in the best interest of the participant to withdraw.vii.The patient has fulfilled the SirAE criteria and completed their IrAE ad hoc visit.

### Statistical considerations

The primary objective of the study is to generate pilot data from a substantive cohort to support hypotheses that may be tested and/or validated in future investigations. Statistical considerations are applied to address secondary (hypothesis testing) and exploratory (hypothesis generating) objectives.

#### Sample size justification

Observations made in a separate study, BIOFLARE [26], on pSTAT3 expression in a subset of circulating CD4 + T cells of RA patients in remission who develop disease flare following treatment cessation *versus* those who do not, were used as a basis for sample size calculation. Assuming CPI recipients with and without SirAEs will display a difference of similar magnitude in CD4 + T cell pSTAT3, enrolment of 66 participants with complete datasets will afford MEDALLION 80% power to detect a difference of ~ 24% between groups at alpha 0.05 (*pilot data used currently in preparation for publication; personal communication, [name] and [name]*). However, the longitudinal nature of our study is an important aspect, as it will allow taking account of the exact time the IrAEs occur. There are very few relevant similar datasets but one recent report found in a Swiss population three immune-related predictors of IrAEs in melanoma patients treated with CPIs: CXCL10, IL-10 and regulatory T cell (Treg) levels with hazards ratios of 12.6, 4.0 and 3.4, respecitvely [27]. Detecting effect sizes broadly similar to these with power 80% at significance level 0.05 requires a minimum of 21 events. Based on the anticipated 32% participants experiencing SirAEs, recruitment and following up of the aforementioned 66 patients will be sufficient for such analyses.

#### Analysis plan

A broad range of measurable immune parameters will be evaluated in MEDALLION, in addition to the microbiome, but the aim of the main statistical analysis (secondary study objective) is to addresses the hypothesis that pSTAT3 expression in circulating CD4 + T cells pSTAT3 predicts SirAE development. The study design ensures that, in addition to testing a specific hypothesis, our unique cohort will form a substrate for a wide range of exploratory analyses in relation to cellular immunity and the microbiome during the development of SirAEs. Descriptive statistics will be used to describe recruitment rates, reasons for refusal to participate, refusal rates for optional procedures and missing data. They will also be applied to compare baseline circulating CD4 + T cell pSTAT3 between patients developing a significant SirAE *versus* those that do not (e.g. Mann-Whitney U test), with similar comparisons made up to the time of incident SirAE or matched time point. Exploratory analyses in relation to other biological parameters will then be undertaken in a similar manner. Markers’ association with time-to-SirAE will furthermore be evaluated using Cox proportional hazards regression. Significantly predictive markers will be graphically displayed by Kaplan-Meier curves after dichotomisation. Mixed effect logistic regression, a form of general linear mixed model (GLMM), will be applied to repeated measurements to test association between SirAE occurrence and marker longitudinal trends. Statistically significant trends will be depicted graphically. GLMM framework is flexible and will allow to exploratively adjust key clinical covariates although their number will be limited by available sample size.

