### Study objectives

The study’s primary objective is to establish a clinically well-characterised and immune-phenotyped inception cohort of patients with cancer commenced on immune CPI therapy, thereby enabling the study of immune dysregulation that precedes IrAE development. In order to interrogate mechanisms of IrAE development we will focus on a range of biological measurements at baseline and during therapy, forming the basis of secondary and exploratory objectives. These will include the frequency and activation status of peripheral blood mononuclear cell (PBMC) subsets determined using multi-parameter flow cytometry, the gut and skin microbiome composition, serum cytokine mediators and, where possible, cellular composition of affected tissue.

The secondary objective of the study is to determine whether STAT3 phosphorylation (pSTAT3) in circulating CD4 + T cells of CPI recipients predicts IrAE development at baseline and/or following initiation of treatment.

The exploratory objectives of the study are:

(i)to determine whether baseline and/or dynamic changes in microbiome composition in the skin or gut precede IrAE development in CPI recipients.(ii)to identify immune cellular phenotypes whose dynamic frequency amongst CPI recipients predicts IrAE development.(iii)amongst CPI recipients who develop clinically significant colitis and/or skin dermatoses as adverse reaction(s) to treatment, to characterise immune infiltrates of lesional *versus* non-lesional tissue.(iv)to determine whether circulating cytokine profiles of CPI recipients predicts IrAE development at baseline and/or following initiation of treatment.

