### Study design

MEDALLION is a single centre, prospective, longitudinal observational cohort study undertaken from the Northern Centre for Cancer Care, Newcastle upon Tyne, UK. All enrolled participants will receive treatment with combination or single agent CPI therapy routinely as standard care, remaining under study follow up for up to 10 months following CPI commencement or until they develop a “significant IrAE” (SirAE) defined according to pre-determined criteria specific to the affected tissue/organ system - whichever is sooner. In keeping with European Society for Medical Oncology (ESMO) practice guidelines, MEDALLION study-specific SirAE definitions generally align with CTCAE Grade 3, but are modified to reflect the significant impact of certain grade 2 IrAEs on quality of life, for example where warranting treatment with corticosteroids; they are summarised in Table 1.

**Table 1 Tab1:** Grades 2 and 3 IrAE definitions align with ESMO criteria [3]

Organ system(s)	MEDALLION definition of SirAE
Skin	Any grade 3 IrAE or above *or* CTCAE grade *≥* 2 IrAE, warranting topical/systemic steroids and/or (in guidance with consulting dermatologist) warranting diagnostic skin biopsy. *or* Physician-diagnosed new onset vitiligo
Gastrointestinal tract	Any grade 3 IrAE or above *or* Diarrhoea, CTCAE grade *≥* 2 persisting *≥* 3 days, warranting steroid treatment and/or endoscopically/histologically confirmed colitis. (Severity grade 2 is 4–6 liquid stools per day over baseline, or abdominal pain or nausea or nocturnal episodes) *or* CTCAE grade *≥* 2 hepatitis warranting steroids
Endocrine	Any grade 3 IrAE or above *or* Symptomatic autoimmune thyroid disease confirmed biochemically *or* Hypophysitis confirmed biochemically and/or radiologically
Musculoskeletal	Any grade 3 IrAE or above *or* Objectively observed inflammatory arthritis
All other	Any grade 3 IrAE or above

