**Fig. 2 Fig2:**
[figure not shown]
MEDALLION enrolment plan and design. Clinical assessments will take place at all patient visits, planned to coincide with routine hospital visits, and red arrows indicate time points at which 53 ml research bloods will be drawn (providing irAE has not occurred); additional research bloods +/- biopsy will be obtained at the time of incident SirAE)

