### Exclusion criteria

Known pre-existing autoimmune or immune-mediated inflammatory disease requiring immunomodulatory treatment, including (but not limited to) inflammatory bowel disease (Crohn’s disease, ulcerative colitis) autoimmune endocrinopathy or hepatitis, vitiligo and inflammatory arthritis.Received enteral or parenteral steroids within past month (topical, inhaled or intranasal permitted).Previous treatment with CPI therapy.Vaccination within the past 4 weeks, except COVID-19 vaccination permitted.Known chronic infection.Current pregnancy, or pregnancy planned within next 6 months.Inability to provide informed consent and/or undergo any of the procedures mandated by the study.

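### The on-treatment comparisons meant to show that pSTAT3 predicts SirAEs should end at the last sample before onset, not run up to the blood drawn at the SirAE itself

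*Protocol article*

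**What the plan says.** The secondary objective (Study objectives) is to establish whether pSTAT3 in circulating CD4+ T cells "predicts IrAE development at baseline and/or following initiation of treatment". The Analysis plan calls this the main statistical analysis. It will "compare baseline circulating CD4 + T cell pSTAT3 between patients developing a significant SirAE" and those who do not develop one, for example by Mann-Whitney U test, "with similar comparisons made up to the time of incident SirAE or matched time point". Cox regression for time to SirAE and a mixed-effects logistic model for longitudinal trends follow.

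The legend to Fig. 2 states that "additional research bloods +/- biopsy will be obtained at the time of incident SirAE", and Table 2 ticks research blood in the SirAE Visit column. Footnote e to Table 2 prefers to combine the SirAE procedures with the visit at which the SirAE is determined. If a visit already falls inside a 7-day window (14 days with biopsy), it adds "in which instance the SirAE procedures should be carried out alone". It also allows a separate visit where confirmation waits on blood results or a biopsy.

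Steroids appear in several SirAE definitions in Table 1; the skin row, for instance, includes grade 2 events "warranting topical/systemic steroids and/or" biopsy. At entry, recent systemic steroids are an exclusion: "Received enteral or parenteral steroids within past month (topical, inhaled or intranasal permitted". In Table 2, the row "Concomitant meds recording" is ticked in every visit column except the SirAE Visit.

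**The concern.** A predictor has to be measured before the thing it predicts. Blood taken once a patient meets SirAE criteria describes a patient with established toxicity. The Background section of the article itself links IL-6-driven STAT3 signalling to immune-mediated disease, so raised pSTAT3 at that moment could be a consequence of the inflammation. If steroids have started, the value may be altered again, in a direction and by an amount the documents do not give.

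The event sample also exists only in cases. Comparators contribute a scheduled sample at a matched time, when nothing has happened to them. A contrast at that point mixes predictor, disease and possibly treatment. An effect of the event could be reported as a precursor, or a true earlier rise could be hidden.

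**Working it through.** **1. The plan's own figure.** The Sample size justification asks for at least 21 events, with 80% power and alpha 0.05. For the smallest cited hazard ratio, 3.4, Schoenfeld's formula with an even split and two-sided alpha gives 4 × (1.960 + 0.842)² / (ln 3.4)² = 31.40 / 1.498 = 20.96, so 21. The figure reproduces, and this point changes no stated number. The pSTAT3 difference of about 24% cannot be checked because no SD is given. For scale, 21 against 45 (66 − 21) has 80% power for 2.802 × √(1/21 + 1/45) = 0.74 SD, or 0.74 / √0.955 = 0.76 SD for Mann-Whitney.

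**2. Does the window include the event sample?** The comparison window runs to the incident SirAE. A research blood is scheduled there. The clause pairs the event with a matched time point in the other group, which only makes sense if cases contribute a value at the event. Inclusion is therefore the natural reading, though not the only possible one.

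**3. Is the sample at or after onset?** By default it is taken when the SirAE is determined, which is already at or after onset. Three provisions can lengthen the gap:
- The grade 2 diarrhoea criterion in Table 1 needs at least 3 days of symptoms.
- Footnote e allows a separate visit and refers to 7 or 14 days around identification (its wording is unclear).
- Footnote f allows special-case procedures more than 14 days after identification, and research blood is ticked in that column.

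**4. Can it follow steroids?** The Background says many IrAEs receive steroids early, and the grade 2 skin, diarrhoea and hepatitis criteria refer to steroids being warranted. The text permits sampling after steroid start but does not state it. When the SirAE visit is combined with a scheduled or unscheduled visit, that visit's column records medication. When it stands alone, Table 2 schedules no medication record.

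**5. How much could this matter?** This is an illustration under assumed values. Comparators: 45 draws from N(0,1). Cases: 21 draws from N(0,1), so no predictive value, with an event-time shift added to all 21 or to 10 of them. Two-sided Mann-Whitney at 0.05, 4,000 simulated studies; simulation error at most √(0.25/4000) = 0.8 percentage points.

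| Assumed shift (SD) | Rejects, all 21 shifted | Rejects, 10 of 21 shifted |
|---|---|---|
| 0 | 5.5% | 4.7% |
| 0.25 | 14.9% | 5.9% |
| 0.50 | 43.5% | 13.7% |
| 0.75 | 77.8% | 21.1% |
| 1.00 | 94.8% | 36.5% |

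A downward shift rejects equally often in this setting. Where pSTAT3 truly is raised before the event, a downward shift would work against detecting it.

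**6. Which analyses are touched?** The baseline comparison is not touched, nor are scheduled samples taken before onset. The Cox model is touched only if pSTAT3 enters as a time-updated value that includes the event sample. The mixed model is touched only if that sample is among the repeated measurements. There it would normally be the last regular point in a case's series, because follow-up ends at the SirAE.

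**The case against.** The clause can be read as stopping before the event, so the plan is ambiguous rather than plainly wrong. The comparisons are introduced as descriptive, in a study meant to supply pilot data, and sampling at the event serves the legitimate aim of describing immunity as SirAEs develop. Rules for excluding samples often sit in the full protocol or SAP, which are not shown.

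Part of this stands. The event sample is worth having, and the absence of a sample-exclusion rule is not the point here. But the article does state a window, and it states it for the analysis serving a prediction hypothesis. The two readings of that window answer different questions.

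A reader might infer more than the text supports:
- **That the whole predictive analysis fails.** It does not; the baseline comparison and scheduled pre-event samples remain valid tests.
- **That the event sample is taken on steroids.** Warranted means indicated, not given, and same-visit sampling is the default. Vitiligo, thyroid disease, hypophysitis and arthritis can qualify with no steroid criterion.
- **That steroid timing goes unrecorded.** Every other visit column records concomitant medication, including the special-case column, so the gap is confined to SirAE visits carried out alone.
- **That comparators are contaminated by steroids.** A grade 2 event in an organ system under the last row of Table 1 leaves the patient in follow-up, and such a patient might be treated. No frequency is given, and the scheduled medication record would identify those samples.

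**Conclusion.** The concern holds for the event-time sample only. On its natural reading, the comparison window takes in blood drawn at or after SirAE onset, and a difference in that blood cannot support a claim of prediction. Up to one sample per SirAE patient is affected, about 21 on the plan's count.

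The size of any bias is unknown, because the documents give no effect of toxicity or steroids on pSTAT3; it could go either way. The simulated rates rest on assumed shifts and show what is possible, not what this study will produce. They do show that a shift close to the difference the study can detect (about 0.75 SD), if present in every event sample, would give a significant result in roughly three of four studies with no prediction at all. The conclusion also rests on reading the window as including the event; if it was meant to stop earlier, the wording should say so.

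**What to change.** - **Predictive analyses.** End the on-treatment group comparisons, any time-updated Cox model and the longitudinal mixed model at the last sample before SirAE onset, with comparators matched on time since CPI start.
- **Event sample.** Report it separately as an at-onset comparison, flagged by systemic steroid exposure, and not as evidence of prediction.
- **Sensitivity analysis.** Repeat without samples taken after systemic steroids, in either group.
- **Data capture.** Tick concomitant medication, with steroid start date, in the SirAE Visit column of Table 2, so that visits carried out alone are covered.

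The cost is a change of analysis wording and one data field, with no effect on recruitment or on how patients are managed. The loss is that event-time samples leave the predictive analysis. A patient whose SirAE comes before visit 2 (week 3, 4 or 6, depending on regimen) would contribute baseline only.

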## Discussion

Developing understanding of the pathogenesis of IrAEs is fundamentally important to attempt to predict and effectively target toxicity within the CPI-treated population. The mechanistic insights this could provide for other IMIDs is also important, due to probable shared disease pathways and difficulty examining the early pre-symptomatic phase of IMIDs.

The design of the MEDALLION study allows for close monitoring during the period in which IrAEs are most likely to arise, without creating any additional visit burden for patients, which was well received by our patient & public involvement group. Within the study, clinical progress over time including; CRP, ESR, neutrophil & lymphocyte counts are captured alongside thyroid, haematological, renal and liver function to identify any subclinical biochemical toxicity. During each participant visit, blood taken for research is processed according to the study SOPs and stored and tracked using a laboratory inventory management system (LIMS).

Future planned analysis of this blood will allow multiple questions to be explored. Deep immune-phenotyping will be undertaken via flow cytometric analysis from whole blood and PBMCs, including investigation of cytokine levels. Stool samples and skin swabs will undergo 16 S rRNA sequencing to determine bacterial and fungal microbiome composition, allowing for comparison between the group developing IrAE and those without. In downstream work, additional sampling in MEDALLION will permit genotyping and epigenetic profiling of residual PBMCs and/or whole blood as well as histological and molecular characterisation of gastrointestinal or dermatological tissue samples collected at SirAE timepoints, with the potential for single cell sequencing of these specimens.

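### On-treatment samples taken while the same toxicity is already present below the SirAE threshold count as preceding the event, so an early sign can be reported as a predictor

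*Protocol article*

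**What the plan says.** The Study objectives describe an inception cohort, "thereby enabling the study of immune dysregulation that precedes IrAE development". The secondary objective asks whether CD4+ T cell pSTAT3 predicts IrAE development at baseline and/or after treatment starts.

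The event analysed is the SirAE. Table 1 sets criteria by organ, and several are met only some way into a toxicity. Grade 2 diarrhoea must persist for at least 3 days and also need steroids or be confirmed as colitis. One endocrine criterion is "Symptomatic autoimmune thyroid disease confirmed biochemically". For a definite IrAE short of the criteria, the section on adverse events and the clinical end point says "this will be recorded as a “non-significant IrAE” and the patient will remain in follow-up". Table 2 lists research bloods at all six scheduled visits. Thyroid and liver tests are taken at the same visits, and the Discussion gives their purpose as "to identify any subclinical biochemical toxicity".

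The Analysis plan has three relevant elements:
- After the baseline pSTAT3 comparison it continues "with similar comparisons made up to the time of incident SirAE or matched time point".
- Mixed effect logistic regression "will be applied to repeated measurements to test association between SirAE occurrence and marker longitudinal trends".
- For markers in general, "association with time-to-SirAE will furthermore be evaluated using Cox proportional hazards regression". This sentence does not say whether baseline or on-treatment values enter.

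The article does not date the first sign of the IrAE that later becomes the SirAE, and it does not separate samples taken after that sign.

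**The concern.** Suppose a patient has a grade 1 rash at the week 3 visit and meets the skin SirAE criteria at week 6, or has abnormal thyroid tests at week 6 and symptoms at week 15. Under the stated rule, scheduled samples between those dates are pre-event samples, although the toxicity is already under way. The issue is these scheduled samples, not the one drawn at the SirAE visit itself.

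A marker that only reflects early inflammation would then differ between patients with and without a SirAE and could be called predictive (reverse causation). The Background frames the key question as the transition from homeostasis to pathology, and this ordering error would blur exactly that. It could touch on-treatment pSTAT3, cytokines, cell subsets, and skin and gut microbiome.

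**Working it through.** **The plan's own figure.** The article gives no figure for this point. The nearest is the 21-event minimum for the Cox analysis. Schoenfeld's formula with HR 3.4, two-sided 0.05, 80% power and a 50/50 marker split gives 4(1.960 + 0.842)² / (ln 3.4)² = 31.4 / 1.498 = 21.0. It reproduces. Nothing below changes it, because the endpoint stays the same.

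**How many cases have a sample in the lower-grade phase.** Inputs:
- Onset window of 3-14 weeks for most IrAEs (Background), 11 weeks wide. A uniform spread is assumed.
- Visit weeks from Table 2, footnote b: melanoma combination 3, 6, 9, 15, 39; 4-weekly nivolumab 4, 8, 12, 16, 40; 6-weekly pembrolizumab 6, 12, 18, 24, 36.
- Lag L from first sign to SirAE: not in the documents, assumed to be 1-3 weeks.

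A visit at week v falls between onset and SirAE when onset lies in (v − L, v]. The share is the total length of these intervals inside weeks 3-14, divided by 11.

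| Schedule | L = 1 | L = 2 | L = 3 |
|---|---|---|---|
| Melanoma combination | (1+1)/11 = 18% | (2+2+1)/11 = 45% | (3+3+2)/11 = 73% |
| Nivolumab 4-weekly | (1+1+1)/11 = 27% | (1+2+2)/11 = 45% | (1+3+3+1)/11 = 73% |
| Pembrolizumab 6-weekly | (1+1)/11 = 18% | (2+2)/11 = 36% | (3+3)/11 = 55% |

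The terms are weeks of onset time contributed by successive visits. For combination at L = 3 they come from visits at weeks 6, 9 and 15. If the only delay is the 3-day diarrhoea criterion, L = 3/7 week and the combination share is 2 × 0.43 / 11 = 8%. The shares apply only to SirAEs that have a lower-grade phase.

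**What such samples could do to a test.** This is an illustration under assumptions, not an estimate. The simulation used 21 cases and 45 others (66 − 21), melanoma combination visits, and a marker with no predictive value that rises by 0.5 or 1.0 SD once toxicity is present. Half or all of the cases had the lag, and comparators had no low-grade toxicity. A Mann-Whitney test was applied to the last scheduled sample before the SirAE, which is one reading of the planned comparison. There were 1,500 runs per setting. Rejection at nominal 5% was:
- lag 1 week: 5-10%
- lag 2 weeks: 7-35%
- lag 4 weeks (beyond the range tabulated above): 12-82%
- using the last sample before onset instead, across all settings: 4-6%.

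**The case against.** The best defence is that the event was chosen deliberately. The Analysis plan states its hypothesis as prediction of SirAE, the Abstract speaks of predictors and precursors of SirAEs, and the Discussion explains the threshold by impact on patients and cites their input. A marker that rises during low-grade toxicity and separates those who progress is a genuine precursor of SirAE. This stands, and it is a reason to keep the endpoint. It does not support saying that such a marker precedes IrAE.

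The Fig. 2 caption makes scheduled research bloods conditional on no irAE having occurred. Read literally, that would prevent these blood samples. It conflicts with the follow-up rule and with Table 2, and the article sometimes uses IrAE where SirAE is meant: withdrawal criterion vii ties the IrAE ad hoc visit to fulfilled SirAE criteria. The caption therefore cannot serve as a safeguard. The same looseness means the objectives' wording alone should not carry the argument.

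Patients whose IrAE never reaches threshold sit among the comparators, so low-grade inflammation can occur in both groups and dilute the bias. That also stands, and the simulated rates leave it out. Some Table 1 criteria, such as new vitiligo or observed arthritis, carry no grade or duration requirement, so those events may have little or no lower-grade phase.

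Lastly, this is a condensed article, and a derived date could sit in the full protocol or analysis plan. But the article does state which samples count, namely those up to the incident SirAE, and that rule is what needs qualifying.

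**Conclusion.** The point holds as an inexpensive improvement limited to on-treatment markers: the comparisons up to the SirAE, the mixed models, and any Cox model that uses on-treatment values. Under the assumed 1-3 week lag and uniform onset, about 18-73% (melanoma combination), 27-73% (4-weekly nivolumab) and 18-55% (6-weekly pembrolizumab) of SirAE cases with a lower-grade phase would have a scheduled sample in it. How far this biases results depends on that unknown lag, on the marker's response, and on low-grade IrAEs among comparators. With a 1-week lag and a small rise, the test stays near its nominal level.

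Three stronger readings are tempting and not supported:
- A reader might infer that the main pSTAT3 test or the time-to-SirAE analysis is invalid. Baseline samples precede treatment, and the Cox sentence does not say that on-treatment values enter.
- A reader might infer that SirAE is the wrong endpoint. The article explains the choice, and predicting it is a legitimate aim.
- A reader might divide lag by visit interval and quote 33-100% for 3-weekly visits. The schedules are not evenly spaced (combination goes from week 9 to week 15), and the tabulated shares replace that figure.

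**What to change.** Keep the SirAE definition, the endpoint and the time-to-SirAE analysis, and add the following.

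1. For each SirAE, derive the date of the first same-organ IrAE of any grade, including a first abnormal thyroid or liver test judged probably or definitely related.
2. For on-treatment comparisons, mixed models and any Cox model with on-treatment values, add an analysis restricted to samples before that date, with matched time points for comparators. Base any claim that a marker precedes or predicts IrAE on this analysis.
3. Report samples between onset and SirAE separately as a transition phase, informative about progression to SirAE.
4. State whether the Cox models use baseline or on-treatment values.
5. Reconcile the Fig. 2 caption with the follow-up rule for non-significant IrAEs and with Table 2.

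The cost is one derived variable and some wording. Adverse events are already graded and related to therapy at each visit, and thyroid and liver tests are taken at every scheduled visit. The real price is fewer on-treatment pre-event samples per case, and so lower precision in the restricted analysis.
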